#### b. 6.2 Study duration

All patients presenting with FMT-HVD bitten by a *Bothrops* snake will be submitted to the standard evaluation. Selected participants will be randomized to one of three treatment regimens at the time. The treatment period will last for 3 days, with 3 days of laser application. The study will run from January 2019 to July 2021.

After the follow-up of the study, the patient will be instructed to seek the study center at any time if they have a complaint related to the snakebite.

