## 7. PATIENT SELECTION

### 7.1. Number of patients planned

The research patients will be allocated into 2 main arms:

- **Arm 1:** Thirty patients bitten by *Bothrops* snakes who received regular FMT treatment.

[figure not shown][figure not shown]

- 
- **Arm 2:** These patients will receive the laser within 30 minutes after administration of the antivenom serum at a dose of 4 J/cm^2.

**First phase T1** - first laser application and first clinical evaluation will take place as follows:

- **Arm 1**, considered control, will receive the conventional treatment from the date of admission to the hospital and will also receive the laser, but turned off, therefore without any effect.
- **Arm 2**, will receive the laser within 30 minutes after administration of the antivenom serum at a dose of 4 J/cm^2.

**Second phase T2** - The groups will receive the same laser therapy regimen to which they were randomized within 24 hours.

**Third phase T3** - 48 hours after the first application. On the 3rd day, the patient is discharged from the hospital if they are well.

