### **8.3. Clinical monitoring of participants**

During this period, clinical (1x/day) and laboratory (1x/day) examinations will be performed daily. Considering the national recommendation, this study will classify the patient according to the local aspects of the lesion for laser application:

| Local Aspects | Edema    | Pain
(numerical
scale) | Temperature
(contralateral
difference) |
|----------------------|-----------------|---------------------------------------|-------------------------------------------------------|
| Light                | 1 to 2 segments | 0-3                                   | Up to 0.5 °C                                          |
| Moderate             | 3 to 4 segments | 4-7                                   | 0.6-1 °C                                              |
| Severe               | 5 segments      | 7-10                                  | More than 1 °C                                        |

\* ADAPTED (38).

c. Participants in arms 1 and 2 will receive clinical evaluation and classification and tests related to inflammation and myonecrosis will be performed during the 3 days of hospitalization.

d. For the evaluation, a clinical form will be used with data on local and systemic signs and symptoms, daily evolution of the patient, evaluation of the wound site at all verification times, demographic data and laboratory tests, and laser application. (see Appendix A).

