## 9.2 Secondary

### Prevention of myonecrosis

Efficacy should be evaluated according to the results of creatine kinase (CK) in the follow-up period (see Appendix A).

- The increase in CK indicates myonecrosis, which should be investigated from the first moment with the patient and after 24 h, 48 h and 72 h. When the patient returns on the 7th day, CK testing will also be performed and evaluated in the two arms of the clinical trial.

Other secondary parameters include:

- Proportion of any adverse events, such as itching, skin redness, changes in skin pigmentation, bruising, scarring, peeling, skin depression, and textural and thickness changes.

[figure not shown][figure not shown]

---

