#### 12.1.1 Inclusion visit: D1, D2, D3

On the first day (**D1**), the patient is seen and randomized to one of the 2 groups.

- In Arm 1, patients will be part of the control, where after completing the clinical form, the signs and symptoms and collection of laboratory tests, they will receive the application of the low-power 4J laser at the site of the snakebite, but turned off.

- In Arm 2, patients, after completing the clinical form, the signs and symptoms and collection of laboratory tests, will receive the application of a low-power 4J laser at the site of the snakebite 30 minutes after the infusion of Antivenom (AV).

On the second day (**D2**), 24 hours after the first application, patients were randomized:

[figure not shown][figure not shown]

---

- In Arm 1, the control patients, after verifying the signs, symptoms and collection of laboratory tests, will receive the application of a low-power 4J laser at the site of the snakebite, but turned off.

- In Arm 2, patients will receive after the signs, symptoms and collection of laboratory tests, will receive the application of low- power laser in 4J at the site of the bite.

On the third day (D3), 48 hours after the first application, patients were randomized:

- In Arm 1, the control patients, after verifying the signs, symptoms and collection of laboratory tests, will receive the application of a low-power 4J laser at the site of the snakebite, but turned off.

- In Arm 2, patients, after verifying the signs, symptoms and collection of laboratory tests, will receive the application of a low-power 4J laser at the site of the bite.

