### 13.2 Statistical and analytical plans

Feasibility outcomes were analyzed using descriptive statistics as proportions. Trial outcomes were reported as means and standard deviations. We report the outcomes using means and standard deviations, and we conducted inferential analysis on our data in order to report the differences between the two groups. Mean values of creatine phosphokinase activity, pain intensity, circumference measurement ratio, extent of edema, difference between the bite-site temperature and that of the contralateral limb, and disability assessments, were compared using the t-test for independent samples, at 48 hours after admission. A Kaplan-Meier survival analysis with a log-rank test was performed to detect differences in the time elapsed from admission to the day of reduction by 50% in creatine phosphokinase activity, pain intensity, circumference measurement ratio, extent of edema and difference between the bite-site temperature and that of the contralateral limb between the intervention and comparator groups, at two points - on 24 and on 48 hours after admission. The comparison of the frequency of use of analgesics, secondary infections and necrosis in a follow-up of 48 hours, between the intervention and comparator groups, was made using the Chi-square or Fisher's exact test; odds ratios with 95% confidence intervals were obtained. The Kruskal-Wallis rank sum test was used to compare the disability scores between groups, for each domain score and for the summary score. Statistical analyses were performed in the R software in the IDE Rstudio environment (version 4.1.2), and the significance level of the tests was 0.05.

[figure not shown][figure not shown]

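### The timed between-arm tests in section 13.2 stop at 48 h, so they reflect two of the three laser applications, and necrosis and infection counts include no follow-up of the third

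*Protocol*

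**What the plan says.** Section 6.2 sets the regimen: "The treatment period will last for 3 days, with 3 days of laser application". Section 7.1 places the third phase "48 hours after the first application", and section 12.1.1 gives the same interval for D3. In the laser arm the first application comes after the clinical form, the blood sample and the antivenom infusion (sections 7.1 and 12.1.1).

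On D3 the order is assessment first, laser second: "In Arm 2, patients, after verifying the signs, symptoms and collection of laboratory tests, will receive the application of a low-power 4J laser". The control arm follows the same order with the device switched off. Section 8.3 provides one round of each examination per day: "clinical (1x/day) and laboratory (1x/day) examinations will be performed daily".

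Section 13.2, repeated in the Synopsis, then fixes when the arms are compared:

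- The means of CK and the local signs "were compared using the t-test for independent samples, at 48 hours after admission".
- The log-rank comparisons of time to a 50% reduction are made at 24 and 48 h after admission.
- The chi-square or Fisher comparisons cover analgesic use, "secondary infections and necrosis in a follow-up of 48 hours".
- The Kruskal-Wallis test of disability has no stated time.

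Section 9.2 looks further. A rise in CK, taken there as the sign of myonecrosis, "should be investigated from the first moment with the patient and after 24 h, 48 h and 72 h", and CK is measured again at the day 7 return and assessed in both arms. Attachment C has D4 and D7 laboratory columns.

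**The concern.** The treatment schedule and the analysis schedule start from different clocks. Applications are timed from the first application, and the tests are timed from admission. Both use the figure of 48 h, which hides that the last application falls after the last reading.

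Two things are at stake. First, a reader of the results would take the 48 h comparison as evidence on the three-application regimen, when it is evidence on two applications. Second, the protocol makes absence of myonecrosis its clinical tolerability criterion (Synopsis and section 5.1) and marked myonecrosis a reason to stop the study (section 7.5). Yet the planned necrosis and secondary-infection counts close before anything that follows the third exposure can be seen.

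**Working it through.** The protocol states no power, effect size or SD, so there is no figure to reproduce. The check is one of timing.

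**Inputs.** Let t be the hours from admission to the first application in the laser arm. Because antivenom comes first, t > 0 (sections 7.1 and 12.1.1). The second application is 24 h after the first, and the third is 48 h after the first (section 12.1.1). The tests are at 24 h and 48 h after admission (section 13.2).

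**Step 1: applications on the admission clock.** The first is at t, the second at t + 24, and the third at t + 48. The protocol does not give t. For assumed values of 0.5, 1, 2 and 4 h, the third application falls at 48.5, 49, 50 and 52 h after admission.

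**Step 2: applications before each reading.**

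- 48 h reading: the first and second come before it (for any t under 24 h). The third does not, because t + 48 > 48 for every t > 0. That is 2 of 3.
- 24 h reading: only the first comes before it, because t + 24 > 24. That is 1 of 3.

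**Step 3: the looser reading.** Suppose 48 h simply means the D3 visit. Section 12.1.1 puts D3 signs, symptoms and sampling before the D3 laser or sham in both arms, and section 8.3 gives one clinical and one laboratory examination per day. The count is still 2 of 3.

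**Step 4: necrosis and infection window.** Section 13.2 does not say when its 48 h follow-up starts. If it starts at admission, it closes t hours before the third application. If it starts at the first application, it closes when the third is due. Either way, follow-up after the third application is 0 h.

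**Step 5: what the planned CK samples would add.** Taken 72 h after first contact, CK comes 72 − (48 + t) = 24 − t hours after the third application. With the assumed t of 0.5 to 4 h, that is 23.5 to 20 h. The D7 sample comes 7 − 3 = 4 days after D3. Both follow all three applications, and section 13.2 names no test for either.

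**Exceptions.** Thermography is also done after each application (section 8.1), so a temperature taken after the third one may exist. Section 13.2 does not say which reading is compared, and that one would be immediate and later than 48 h after admission.

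**The case against.** **Section 9.2 already plans late CK in both arms.** This stands. It would be wrong to infer that nothing is evaluated after the third application, or that section 13.2 forbids later CK analyses. An analysis plan that is not shown may name a test. What remains is that section 13.2 does not leave the time open: it fixes CK testing at up to 48 h.

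**No time point isolates the third application.** This also stands. With three active against three sham applications, a later comparison evaluates the whole regimen but cannot show what the third application adds.

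**48 h is a defensible choice.** The objective concerns acute local manifestations, patients who are well leave on day 3 (section 7.1), and in-hospital data should be nearly complete. This is a good reason to keep 48 h.

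**A reader might infer a definite loss of power.** The documents do not support that. Take 30 per arm, two-sided 5%, and an assumed full-course effect that gives 80% power. Power at 48 h is then 80% if the third application adds nothing, 65% if it contributes one sixth of the effect, and 46% if it contributes one third. Both the effect and its build-up are assumptions. If controls also recover by day 7, the difference between arms could shrink with time instead.

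**A reader might infer that the main comparison of pain and edema should move to day 7.** That does not follow. Sections 6.2 and 11 describe return after discharge as prompted by complaints, and the visit scheme text in section 12.1.1 stops at D3. The D7 form columns are weak evidence of a schedule, because Attachment A also has a D7 column for laser therapy, which no section plans. A main comparison among patients who choose to come back risks selective missing data.

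**Safety is not wholly cut off at 48 h.** Section 10.2 has adverse events described in both arms during follow-up, and late CK is the protocol's own marker of myonecrosis. Section 4.1 also notes that necrosis may be evident within 24 h. The gap is confined to the formal necrosis, infection and analgesic comparisons.

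**Conclusion.** The timing point holds on the written schedule. It needs only that the first laser application follows admission and that D3 assessment precedes D3 treatment, and the protocol states both. The timed comparisons in section 13.2 cover two of three applications at 48 h and one of three at 24 h. The necrosis and infection counts have no follow-up after the third.

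The consequence is one of interpretation and of an incomplete safety comparison. The 48 h contrast is unbiased by design and remains useful, but it does not evaluate the full regimen. No loss of power can be put on it. The change is worth making because it is cheap and alters what the trial can conclude; it is not a reason to discard the 48 h analysis.

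**What to change.** In section 13.2 and the matching Synopsis text:

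1. Keep the 48 h comparisons and state that they follow two applications.
2. Count time from the first application or sham in both arms, so that the analysis and treatment schedules share one clock.
3. Add a between-arm comparison of CK at 72 h and at day 7, which section 9.2 already requires to be collected.
4. Extend the necrosis and secondary-infection counts to the day 7 return, and report the number assessed in each arm.

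Sections 6.2 and 11 should say that the day 7 return applies to every patient, as section 9.2 implies, and not only to those with a complaint.

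The cost is protocol wording plus a wound check at the day 7 return. Some late data will be missing, since patients may leave on day 3; reporting the number assessed per arm makes that visible. Pain and edema can stay at 48 h as planned.

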|                                                  |                                                                                                                                                                                                                                                                                                                                                                                                                                                                                                                                                                                                                                                                                                                                                                                                |
|--------------------------------------------------|------------------------------------------------------------------------------------------------------------------------------------------------------------------------------------------------------------------------------------------------------------------------------------------------------------------------------------------------------------------------------------------------------------------------------------------------------------------------------------------------------------------------------------------------------------------------------------------------------------------------------------------------------------------------------------------------------------------------------------------------------------------------------------------------|
| 
Expected total number of patients:
 | 
d) Patient is immunocompromised;
e) Patient is on a course of anti-inflammatories or antibiotics;
f) Patient has diabetes mellitus (DM).
 
60 patients, 30 in the treatment group and 30 in the control group, stratified as follows:
 
Arm 1) Considered the control group, this arm will receive conventional treatment from the date of admission to the hospital and will also receive the protocol with the laser turned off, therefore without any effect.
 
Arm 2) This arm will receive the laser treatment within 30 minutes after the infusion of antivenom serum at a dose of 4j/cm^2.
                                                                                                                                                      |

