| 
EVALUATION SCHEME
          | 
Patients will be evaluated with the same parameters irrespective of the group to which they were allocated at the time of admission, and at 24 and 48 hours in relation to clinical and laboratory aspects.
                                                                                                                                                                                                                                                                                                                                                                                                                                                                                                                                                                                                                                                                                                                                                                                                                 |
| 
STATISTICAL CONSIDERATIONS
 | 
Number of patients:
 
A priori, 60 patients in order to evaluate the effectiveness and safety of low-intensity laser in sites of snakebites involving the genus Bothrops.
 
Statistical generalities:
 
This study foresees the performance of an interim analysis when the groups reach half of their recruitment, i.e., 15 patients in each group. This analysis will be able to identify variations related to the primary outcome and will indicate the need for continuity, restructuring, or finalization of the study. Quantitative variables will be calculated for frequency and proportions, with the calculation of means.
 
Feasibility outcomes were analyzed using descriptive statistics as proportions. Trial outcomes were reported as means and standard deviations. We report the outcomes using means and standard deviations, and we conducted inferential analysis on our data in order to report the differences between the two groups. Mean values
 |

[figure not shown][figure not shown]

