## 5. STUDY OBJECTIVES

### 5.1 Primary

To evaluate the effectiveness of low-power laser in the recovery of acute local manifestations in victims of *Bothrops* envenomations.

Clinical and biological tolerability:

- Clinical tolerability: No appearance of myonecrosis.
- Biological safety: CK (creatine kinase).

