## 6. STUDY DESIGN

### 6.1. Protocol description

A 2-arm, double-blind, randomized, safety, phase II clinical trial conducted at one center in Brazil.

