## **8.2. Method of assigning patients to the group and blinding**

A randomized clinical trial is a prospective study in humans comparing the effect and value of an intervention against a control.

Randomized clinical trials should be considered when:

- A. There is uncertainty about the effect of an exposure or treatment;
- B. Exposure can be modified in the study.

Potential limitations of randomized controlled trials include:

- A. Limited generalizability of the study population.
- B. Limited generalization of the environment under study.
- C. Randomized clinical trials answer a specific study question.

The usual measures of the magnitude of effect in randomized clinical trials are relative risk and risk difference.

The method that will be used in the measurement of the research is double masking (double-blind). This implies that neither the patient nor the professional doing the evaluation knows which treatment is being given. The double-blind method tries to eliminate evaluation bias.

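### Odds ratios with 0.05-level tests are the only formal comparison of necrosis and infection in a trial labelled safety; they cannot bound excess harm when the control arm has no events, and a risk difference with its interval could

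*Protocol*

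**What the plan says.** Section 6.1 describes the design as "A 2-arm, double-blind, randomized, safety, phase II clinical trial conducted at one center in Brazil". The synopsis plans "60 patients in order to evaluate the effectiveness and safety of low-intensity laser", allocated as "60 patients, 30 in the treatment group and 30 in the control group". Section 5.1 puts two tolerability criteria under the primary objective: "Clinical tolerability: No appearance of myonecrosis", and creatine kinase (CK).

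Section 13.2, repeated in the synopsis, fixes the formal analysis. For the binary outcomes it reads "The comparison of the frequency of use of analgesics, secondary infections and necrosis in a follow-up of 48 hours", between the two groups, "was made using the Chi-square or Fisher's exact test; odds ratios with 95% confidence intervals were obtained". Mean CK at 48 hours is compared by an independent-samples t-test, and time to a 50% fall in CK by a log-rank test. For all of these, "the significance level of the tests was 0.05".

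Section 8.2, in general remarks on randomised trials, says: "The usual measures of the magnitude of effect in randomized clinical trials are relative risk and risk difference". Section 13.2 uses neither measure.

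Other safety provisions exist. Section 10.1 bases safety on registered adverse events, graded laboratory results and vital signs. Sections 9.2 and 10.2 have adverse events given as proportions and described in both arms. Section 7.5 lets marked myonecrosis lead to the study being discontinued. None of these sets a numerical limit on excess harm.

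**The concern.** A safety question asks how much extra harm is still compatible with the data. A difference test at 0.05 answers another question, and with 30 per arm it will often be non-significant whether or not the laser worsens local damage. The effect measure placed beside the test ought to fill that gap. The odds ratio does not do so when events are few, and no necrosis at all is the result the tolerability criterion hopes for. At stake is whether the report of a safety trial can say how large an excess of necrosis or infection it has excluded.

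**Working it through.** **Inputs.** From the protocol: 30 per arm (synopsis), significance level 0.05 (13.2), Chi-square or Fisher with odds ratios (13.2). Not given and therefore assumed: two-sided testing, and a control-arm necrosis rate between 5% and 30%. The total of 60 cannot be reproduced, because no power, effect size or event rate is stated.

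**Step 1: chance of missing a true doubling.** For control rate p and laser rate 2p, sum the product of the two binomial(30) probabilities over all 31 × 31 outcomes in which the test gives p < 0.05 with more events on laser. The miss rate is one minus that sum.

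| Control → laser | Fisher | Uncorrected Chi-square |
|---|---|---|
| 5% → 10% | 98% | 90% |
| 10% → 20% | 90% | 81% |
| 15% → 30% | 81% | 72% |
| 20% → 40% | 70% | 61% |
| 25% → 50% | 59% | 48% |
| 30% → 60% | 44% | 34% |

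For CK by t-test with 30 per arm (noncentral t, 58 degrees of freedom), a true rise of 0.5 SD is missed 52% of the time and one of 0.75 SD 18.5% of the time.

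**Step 2: what the odds ratio gives with empty cells** (laser v control events, 30 per arm).

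- 0 v 0: undefined.
- 3 v 0: infinite estimate; exact 95% interval 0.42 to infinity.
- 5 v 0: infinite estimate; exact interval 0.98 to infinity.
- 0 v 3: estimate 0; exact interval 0 to 2.37, a usable upper limit.

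Adding 0.5 to each cell gives a finite interval, but for 3 v 0 it runs from 0.38 to 157, an upper limit of no practical use.

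So the upper limit on harm is lost exactly when the control arm is empty, whatever happens on laser. That has probability (1 − p)^30:

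- p = 3%: 0.97^30 = 40%
- p = 5%: 0.95^30 = 21%
- p = 10%: 0.90^30 = 4%
- p = 15%: 0.85^30 = 0.8%

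**Step 3: what the risk difference gives.** With d the observed difference and (l, u) the Wilson 95% limits in each arm, Newcombe's interval is

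lower = d − √[(p_L − l_L)² + (u_C − p_C)²], upper = d + √[(u_L − p_L)² + (p_C − l_C)²].

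- 0 v 0: Wilson limits 0 to 3.841/(30 + 3.841) = 0.114 in each arm, so the interval is ±11 points.
- 3 v 3: Wilson limits 0.035 to 0.256; √(0.156² + 0.065²) = 0.169, so ±17 points.
- 5 v 0: d = 0.167; Wilson limits 0.073 to 0.336 and 0 to 0.114. Lower = 0.167 − √(0.093² + 0.114²) = 0.020; upper = 0.167 + 0.169 = 0.336. The interval is +2 to +34 points.

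The 5 v 0 case shows the practical difference. The expected count is 5 × 30/60 = 2.5 per arm, so Fisher would normally be chosen, and it gives p = 0.052 with an infinite odds ratio. (The uncorrected Chi-square gives 0.020; section 13.2 does not say which test applies when.) The risk difference shows the signal and bounds its size.

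**The case against.** Several stronger readings are tempting, and the protocol does not support them.

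- *Non-significance will be reported as safety.* A reader might infer this from the absence of a harm margin, but no section says it.
- *Safety is judged by tests alone.* It is not: sections 7.5, 9.2, 10.1 and 10.2 add description, grading and a discontinuation criterion, and 13.2 plans confidence intervals. Only the formal between-arm comparison is at issue.
- *A doubling is missed 80–90% of the time.* That holds for Fisher only at control rates of about 10–15%. Section 4.1 speaks of high prevalence without a figure, which if anything points to higher rates and lower miss rates.
- *The odds ratio fails whenever an arm is empty.* It does not when only the laser arm is empty. At the 10–15% rates just mentioned, an empty control arm is also rare (about 1–4%), so the two problems are not at their worst together.

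The planned interval would also often reveal imprecision. For 9 v 3 events Fisher gives p = 0.10, and the exact odds ratio interval, 0.81 to 24.4, would hardly be taken as proof of safety. Necrosis and CK have an efficacy role as well (section 9.2 treats prevention of myonecrosis as an efficacy outcome), and a difference test suits that role. The remark in 8.2 on usual measures is general text, not a commitment that 13.2 breaks. Interval methods are commonly left to a statistical analysis plan, which may exist.

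All of this narrows the point without removing it. Section 13.2 itself fixes the test, the level and the effect measure, and that measure cannot bound excess harm when the control arm has no events.

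**Conclusion.** The point holds as an inexpensive improvement to the stated method. For necrosis and secondary infection, the only formal comparison is a 0.05-level test with an odds ratio. Under assumed control rates of 5% to 30%, a doubling is missed 98% to 44% of the time by Fisher and 90% to 34% by the uncorrected Chi-square, so a non-significant test carries little information about safety. The odds ratio gives no usable upper limit on harm when the control arm is empty: 21% of trials at a 5% rate and 4% at 10%. The risk difference gives a bound in each of these cases. The miss rates and empty-arm probabilities rest on assumed rates and two-sided testing; the behaviour of the two measures with empty cells does not. Low power by itself is not the defect, since the protocol claims no power for safety.

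**What to change.** In section 13.2 and the matching synopsis text:

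1. Make the risk difference (laser minus control) with a 95% Newcombe or Miettinen-Nurminen interval the main safety summary for necrosis and secondary infection. Keep Fisher's test and the odds ratio as supplementary output.
2. Report the between-arm CK difference or ratio with its 95% confidence interval.
3. State that a non-significant test is not evidence of safety.
4. State that 30 per arm excludes only an excess above about 11 points if neither arm has an event, or about 17 points with three events in each, so the safety assessment is preliminary.

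The cost is a few sentences and a few lines of R. No patients, visits or data are added, and no clinical rule changes. The downside is a more modest safety statement.
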